## Abstract

**Objectives:**

Chronic low back pain has become a major cause of global disability and caused a huge economic burden to society. Physical therapy is a vital strategy for rehabilitation of chronic low back pain. Although several trials have shown that Tai Chi Quan is a beneficial treatment, the comparative effectiveness of Tai Chi Quan versus physical therapy is unknown. We are conducting a randomized controlled trial to assess the effectiveness of Tai Chi Quan versus that of physical therapy in treating chronic low back pain.

**Methods:**

We will perform a single-blind randomized controlled trial on elderly people with chronic low back pain. 138 participants will be randomly assigned to the Tai Chi Quan group (60-min classes, three times per week for 12 weeks) or physical therapy group (10 min of evaluation and warm-up, 40 min of therapist-directed exercise therapy, and 10 min of relaxation, three times per week for 12 weeks) with an allocation of 1:1. The participants will be followed up for 40 weeks for the study of long-term effects. The primary outcomes include pain intensity and back-related function at 12 weeks. Secondary outcomes include lumbar quantitative sensory testing, balance, cognitive function, psychosocial function, cost-effectiveness, compliance and adverse events. We will perform the intention-to-treat analysis for withdrawal and missing data.

**Discussion:**

The study will be the first randomized trial with comparative-effectiveness of Tai Chi Quan and physical therapy for chronic low back pain. Standardized protocol, large sample size, and comprehensive outcomes are important features in this trial. This study aims to determine the feasibility and effectiveness of Tai Chi Quan for low back pain. The results of this study will be beneficial for elderly people with low back pain and medical rehabilitation personnel.

**Clinical Trial Registration:**

www.chictr.org.cn, identifier ChiCTR2000029723.

## Introduction

Low back pain (LBP) is a common pain syndrome between the lower rib margins and buttock creases and occurs at all ages (Hartvigsen et al., 2018). When LBP lasts more than 3 months, it is called chronic low back pain (CLBP), which is more common in women and the elderly (Hoy et al., 2012). By 2017, LBP has prevailed as one of the leading causes of global years lived with disability (YLD) and non-fatal health loss (GBD 2015 Disease and Injury Incidence and Prevalence Collaborators, 2018), and YLD increased by 54% between 1990 and 2015, especially in low- and middle-income countries (GBD 2015 Disease and Injury Incidence and Prevalence Collaborators, 2016). The prevalence of LBP is more than 80%, of which CLBP accounts for 23%, and the disability rate is 11–12% (Brinjikji et al., 2015; Maher et al., 2017). The prevalence of LBP ranged from approximately 28 to 51% in 28 countries (Maher et al., 2017). A systematic review of 35 studies found that the prevalence of LBP ranged from 21 to 75% among approximately 130,000 people aged over 60 years, and the majority of patients had functional disabilities and limitations of physical capacity (de Souza et al., 2019). Owing to changes in social environment and lifestyle, physical inactivity and sedentarism have become worldwide issues and important predictors of poor health (Panahi and Tremblay, 2018), and the incidence of adolescents with LBP shows an increasing trend (Shim et al., 2014). People with CLBP suffer from unpleasant nociceptive sensation and limited activities, are often absent from work and have low quality of life (Deyo et al., 2014). The cost of LBP ranked sixth in the overall burden of diseases (“Global, regional, and national incidence, prevalence, and years lived with disability for 301 acute and chronic diseases and injuries in 188 countries, 1990–2013: a systematic analysis for the Global Burden of Disease Study 2013 Collaborators, 2015). Studies have pointed that LBP forces older people to leave work and retire early; this situation results in huge indirect costs (mainly lost productivity and household income) (Ferreira et al., 2010). People who retire early because of LBP earn approximately 87% less than people who work full time (Schofield et al., 2011). In 2018, the World Health Organization has identified research on ‘reducing disabling LBP’ as one of its global health priority programs (Buchbinder et al., 2018). LBP is of urgent global public health concern.

The non-invasive management for CLBP usually includes medication, physical therapy (PT) and education about being physically active (Qaseem et al., 2017). PT consists of movement therapy (such as aerobic exercise, whole body vibration exercise, and core stability exercise), manual therapy (such as massage, spinal manipulation, spinal mobilization, and nerve mobilization) and modality therapy (such as electrotherapies, laser therapy, and superficial heat therapy), and the international guidelines for LBP have provided a specific set of recommendations for these three sections (de Campos, 2017; Qaseem et al., 2017; George et al., 2021). Movement therapy has been recognized as a core part of LBP treatment (R. Wang et al., 2020). A systematic review have shown that guided and personalized exercise programs can effectively improve CLBP (Hayden et al., 2005). In clinical randomized controlled trials (RCTs), PT is often compared with other LBP interventions, and cost-benefit analyses are performed. Saper et al. founded that yoga and PT are effective for CLBP after 12-week intervention, and yoga is not inferior to PT in terms of improving lumbar function and relieving pain (Saper et al., 2017). Vibe et al. compared the effects of cognitive function therapy with those of PT for CLBP and showed that PT fully reflects the emphasis on exercise therapy and the importance of classified diagnosis and treatment (Vibe Fersum et al., 2013). Pengel et al. used physiotherapist-directed exercise interventions in patients with LBP, and their pain and physical function scores were significantly better than those of the placebo group after 6 weeks (Pengel et al., 2007). PT plays an important role in musculoskeletal disorders. The national PT referral rate for LBP patients aged 45 to 59 years in the United States between 1997 and 2010 was estimated to be about 36.5%, and the rate was approximately 19% for LBP patients aged 60 and above (Zheng et al., 2017). In the Chinese clinical setting, patients with chronic pain are mostly managed by rehabilitation therapists, and those with high incomes are particularly likely to choose individualized therapists. Although therapist-directed PT is effective in resolving the problems of patients, the cost of PT is considerable for most low- and middle-income people with CLBP. At present, health care staff and patients are looking forward to a long-term effective alternative treatment with lower economic burden.

As a traditional exercise therapy, Tai Chi Quan (TCQ) has been widely used in researching health promotion interventions for posture balance and fall and chronic diseases (Liu et al., 2012; X. Wang et al., 2015; Zhi-lei and Dong, 2018). A systematic review has demonstrated the safety and reliability of the clinical application of TCQ (Wayne et al., 2014). In 2017, the clinical guideline issued by the American College of Physicians strongly recommended TCQ for CLBP (Qaseem et al., 2017). TCQ is considered an active therapy and a coordinated movement in which a practitioner needs to concentrate and coordinate breathing. TCQ involves circular and curved movements, emphasizes the twisting of the waist and hips and drives the limbs into diagonal spiral movements. The forward and backward, left and right and oblique steps can improve the flexibility and stability of the joints (Li, 2014). In recent years, some important achievements about TCQ have been made in health promotion and disease intervention (Li et al., 2012, 2018; C. Wang et al., 2016). In 2011, an RCT of TCQ for persistent LBP found that 10 weeks of TCQ exercise improves pain levels and pain-related disability (Hall et al., 2011). In 2013, Another RCT showed that 6 months of TCQ is effective in reducing pain symptoms and can be used as an alternative therapy (Sun, 2013).

Tai Chi Quan can significantly improve core stability and muscle strength, thereby reducing the risk of falls in patients with CLBP (Lomas-Vega et al., 2017). Sleep problems are common among people with CLBP, and insomnia can increase the risk of CLBP (Skarpsno et al., 2020). A meta-analysis showed that TCQ has a significant beneficial effect on the sleep quality of the elderly (Du et al., 2015). The intensity of TCQ practice depends on time, speed and experience. For the elderly with CLBP, simplified TCQ is easy to learn and can improve balance, coordination and spinal stability. Compared with the waiting group and the usual care group, TCQ from 10 to 28 weeks had a better effect on lumbago (Kong et al., 2016). However, few studies have investigated the long-term follow-up effects of TCQ on CLBP. Although PT is the main management method for LBP rehabilitation, it is expensive in terms of manpower and financial resources. As an easy to learn and low- cost exercise therapy, TCQ is expected to be accepted as an alternative therapy by a large number of patients with CLBP. However, previous studies had some deficiencies, such as short intervention time, lack of follow-up observation and economic analysis, and evidence supporting the application value of TCQ in patients with CLBP remains insufficient. Therefore, we propose a detailed protocol to study the comparative effectiveness of TCQ classes versus grouped-PT for people with CLBP. Our primary hypothesis is that TCQ and grouped-PT have a significant clinical effect on CLBP. The secondary hypothesis is that TCQ is not inferior to PT in terms of improving outcomes. The third hypothesis is that TCQ has a longer-term effect than PT.

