### Sample Size

The sample size analysis is based on hypothesized change in RMDQ scores. For the primary outcome of change in pain intensity from baseline to week 12, we assume that two-sided α error prob is equal to 0.05 and power is 0.8. The minimal clinically important difference of the RMDQ is prespecified for 3 points (Jordan et al., 2006), and the effect size of RMDQ is in the range of 0.54–0.84 (Saper et al., 2017). We used G-Power Software (version 3.1.9.2, Germany) to estimate the total sample size with the method of *t*-tests-means (difference between two independent means measures in two groups). Considering the effect size of RMDQ is 0.54 and 20% attrition rate, we need a minimum of 138 participants in this study or 69 participants in each group to detect whether 12 weeks of TCQ and grouped-PT have a significant clinical effect on CLBP.

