### Data Analysis

Intention-to-treat analysis will be performed regardless of adherence. Microsoft excel 2016 and IBM SPSS Statistics 20.0 (SPSS Inc., Chicago, IL, United States) will be used in data analysis. Continuous variables (e.g., age, body mass index, NRS score, and RMDQ score) will be represented as mean ± standard deviation and be compared using analysis of the independent samples *t*-test. We will use the chi-squared test to analyze the categorical variables (e.g., gender, marital status, smoking, and exercise habits) between the TCQ group and PT group. The baseline demographics characteristics differences between groups will be compared using analysis of *t*-test, variance (ANOVA) or chi-squared tests. If potential confounding factors including gender, age, body mass index, smoking, exercise habits, etc., are present, we will prespecified an adjusted analysis, by using multiple linear regression. At the same time, missing values at week 12, 26, and 52 will be imputed using the multiple imputation.

The co-primary outcomes are the measurement of minimal clinically important difference in NRS and RMDQ scores in two groups after the 12-week intervention, and the paired-sample *t*-test will be carried out for the comparison of the differences. For secondary outcomes, the difference of continuous variables between groups will be compared using the analysis of independent-samples *t*-test. Expenses for LBP or other disease will be explored for cost-benefit analysis. Participants’ global perceived effect, adherence, and health-related quality of life will be compare using appropriate regression. The Fisher exact test will be used to compare adverse events. For the follow-ups phase, two-way repeated-measures analysis of variance (group × time) will be carried out to assess the differences of the primary outcomes (NRS score and RMDQ score) between the two groups. In all analyses, a *P*-value of <0.05 will be considered statistically significant.

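### The hypothesis that Tai Chi Quan is not inferior to physical therapy has no margin or confidence-interval rule, and the planned difference tests at P < 0.05 cannot establish it short of superiority

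*Protocol article*

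**What the plan says.** All of this is in the protocol article.

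- **Introduction, last paragraph.** There are three hypotheses. The first is about both treatments: "Our primary hypothesis is that TCQ and grouped-PT have a significant clinical effect on CLBP". The second is the non-inferiority claim: "The secondary hypothesis is that TCQ is not inferior to PT in terms of improving outcomes". The third is about durability: "The third hypothesis is that TCQ has a longer-term effect than PT". The second and third name no outcome or time point, and the second names no margin.
- **Sample Size.** The calculation is a two-sample t-test for a difference: "we assume that two-sided α error prob is equal to 0.05 and power is 0.8", and then "Considering the effect size of RMDQ is 0.54 and 20% attrition rate, we need a minimum of 138 participants". A minimal clinically important difference (MCID) of 3 RMDQ points is given here. The RMDQ section gives a second version, a 30% reduction from baseline. Neither is called a non-inferiority margin.
- **Data Analysis.** The co-primary outcomes get a paired t-test. Continuous variables are compared between arms by independent t-test, with multiple linear regression if confounders are present. Other outcomes get regression, chi-squared or Fisher tests. For follow-up, "two-way repeated-measures analysis of variance (group × time) will be carried out to assess the differences of the primary outcomes". One decision rule covers everything: "In all analyses, a *P*-value of <0.05 will be considered statistically significant".

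**The concern.** A non-inferiority hypothesis is tested against a null that the new treatment is worse by at least a stated margin. The tests in this plan have a null of no difference. Failing to reject that null says only that the data did not separate the arms, and this can happen when TCQ is worse by an amount that matters.

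Two supervised exercise programmes, each given three times a week, may well perform alike, so a non-significant comparison is a likely result. The Discussion presents the trial as evidence on whether TCQ can serve as an alternative to physical therapy (PT). Without a margin and a rule, the article gives no valid way to turn a non-significant P into that conclusion. A margin chosen after the data are seen can be fitted to the result.

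This is more than a detail left to a statistical analysis plan. The article states alpha, power, effect size, attrition, tests and significance threshold, and those describe a different kind of trial from the second hypothesis.

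**Working it through.** **1. Reproduce the plan's figure.** Inputs from Sample Size: d = 0.54, two-sided alpha 0.05, power 0.80, attrition 20%. The exact noncentral-t calculation for two independent means needs 55 per arm (power 0.801), 110 in total. Then 110 / (1 − 0.20) = 137.5, rounded up to 138. The stated figure reproduces exactly, as the size for a difference test.

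**2. Assumptions for the illustration.** The article gives neither an SD nor a margin.
- Central SD: if the 3-point MCID is taken to correspond to d = 0.54, SD = 3 / 0.54 = 5.56.
- Range: the upper end of the article's effect-size range gives 3 / 0.84 = 3.57. I take 7 as a high value.
- 55 evaluable participants per arm, treated as independent.
- A positive TCQ minus PT difference means that TCQ is worse.

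**3. Confidence-interval width.** Half-width = t(0.975, 108 df) × SD × √(2/55) = 1.982 × 5.56 × 0.1907 = 2.10 points. Under a 3-point margin, non-inferiority would be shown only if the observed difference were below 3 − 2.10 = 0.90. Under a 2-point margin, TCQ would have to be observed at least slightly better (2 − 2.10 = −0.10).

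**4. Difference test and non-inferiority test compared.** The noncentrality parameter is (Δ/SD) × √(55/2), with Δ the true deficit or the margin. The difference test is two-sided 0.05. The non-inferiority test is one-sided 0.025 at zero true difference. Both have 108 df.

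| | SD 3.57 | SD 5.56 | SD 7 |
|---|---|---|---|
| P ≥ 0.05 when TCQ is truly 2 points worse | 17% | 54% | 68% |
| Non-inferiority power, 3-point margin | 99% | 80% | 61% |
| Non-inferiority power, 2-point margin | 83% | 46% | 32% |

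The size needed at SD 5.56, by the normal approximation n = 2(1.96 + 0.84)² SD² / margin², is:
- 3-point margin: 54 per arm, 108 / 0.8 = 135 in total;
- 2-point margin: 122 per arm, 244 / 0.8 = 305 in total.

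**5. The one route that the plan leaves open.** A significant between-arm result favouring TCQ implies non-inferiority at any margin. Its probability with 55 per arm is 2.5% if the arms are equal and 29% if TCQ is better by 0.27 SD.

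**6. Third hypothesis.** The group × time test was simulated with 55 per arm, within-person correlation 0.5 and 3,000 runs. In the durability scenarios one arm keeps a gain of 1 SD while the other falls back to 0.7 and then 0.46 SD.

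| Visits in the model | TCQ lasts longer | PT lasts longer | Constant TCQ advantage of 0.54 SD from week 12 |
|---|---|---|---|
| Baseline, 12, 26, 52 | 81% | 81% | 84% |
| 12, 26, 52 only | 70% | not run | 6% |

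With baseline included, the P-value does not separate the three situations. With post-treatment visits only, the test does bear on durability, but it still carries no direction.

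**The case against.** Several objections have force.

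- **A reader might infer that no result of this trial could establish non-inferiority.** That goes too far: a significant difference favouring TCQ would do so (step 5).
- **A reader might infer that the trial is too small.** The document does not show this. With a 3-point margin and SD 5.56, 138 participants give about 80% power before any clustering. The percentages also move a great deal with an SD that the article does not state. What is certain is the missing margin and rule.
- **A reader might infer that the authors will read P > 0.05 as equivalence.** Nothing in the article says so. The non-inferiority hypothesis is labelled secondary, and the Sample Size section ties the number to the first hypothesis. The risk comes from the absence of any rule, together with the Discussion's talk of an alternative therapy.
- **A reader might put the third hypothesis under the same fault.** It is a superiority-type claim that needs no margin. A difference test at P < 0.05 is the right kind of test, and group × time with data to week 52 is planned. Only the direction and time points are open, and a condensed article may leave those to the full plan.

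What these objections do not answer is the mismatch for the second hypothesis. Every stated test, including the regressions, is judged by P < 0.05, and none is set against a margin. Nor can a margin be inferred, since the article gives two versions of the RMDQ MCID and assigns neither to this use.

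**Conclusion.** The point holds for the second hypothesis. The plan states non-inferiority but is sized and analysed for a difference, so apart from a significant win for TCQ the analysis as written cannot support the claim.

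The scale of the problem depends on the unstated SD. At 5.56 points the t-test would miss a true 2-point deficit in just over half of trials; across 3.57 to 7 points that runs from about one in six to about two in three. Whether 138 participants suffice depends on the margin: probably for 3 points at the central SD, and not for 2 points.

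The figures treat participants as independent. The Randomization and Blinding section allocates four whole communities, so clustering of outcomes would lower the non-inferiority power and widen a correctly computed interval.

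The third hypothesis is a minor clarification.

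**What to change.** 1. Prespecify one justified margin on the week-12 TCQ minus PT difference in RMDQ, no larger than the plan's own 3-point MCID.
2. Conclude non-inferiority only if the upper limit of the two-sided 95% confidence interval lies below that margin in the intention-to-treat analysis. Add an adherent-set analysis as a sensitivity check, because non-adherence can pull the arms together and favour the claim.
3. State the power for that margin, with the SD used and an allowance for community allocation.
4. State that P > 0.05 will not be read as non-inferiority.
5. If no margin can be justified, drop the second hypothesis and describe the comparison as an estimated difference with its interval.
6. For the third hypothesis, name a directional contrast, such as the between-arm difference in change from week 12 to week 52. A plain difference at week 52 would not do, since it could be an advantage already present at week 12.

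The cost is wording and one sensitivity analysis. The stated power may become less favourable, particularly with a margin below 3 points. The margin has to be fixed before outcome data are examined by arm.

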## Study Design and Methods

### Study Design

The study is a single-blinded RCT of TCQ classes or grouped-PT for patients with CLBP (Figure 1. Study flow diagram). Eligible participants will be randomly assigned into the Tai Chi Quan group (TCQG) or physical therapy group (PTG). Both groups will perform exercises for 60 min three times a week for a total of 12 weeks. After the program, 40 weeks of follow-ups will be conducted.

**FIGURE 1 F1:**
[figure not shown]
Study flow diagram.

The coprimary outcomes after the interventions are maximum and average pain intensity measured using a numerical rating scale (NRS) (Williamson and Hoggart, 2005) and back-related function measured using the Roland Morris Disability questionnaire (RMDQ) (Roland and Morris, 1983). The secondary outcomes include lumbar quantitative sensory testing, balance, cognitive function, psychosocial function, cost-effectiveness, compliance and adverse events. Healthcare utilization data, including medical costs, drugs use and cost of TCQ and PT, are tracked to estimate whether TCQ would be more economical and beneficial than grouped-PT exercise. The outcomes and measurement timepoints are presented in Table 1.

**TABLE 1 T1:** Measurements timing for primary and secondary outcomes.

Outcomes variables	Baseline	Week 12	Week 26 (follow-up)	Week 52 (follow-up)
**Primary outcomes**				
NRS – the Maximum Pain	√	√	√	√
NRS – the Average Pain	√	√	√	√
RMDQ – Back-related Function	√	√	√	√
**Secondary outcomes**				
Lumbar quantitative sensory testing	√	√		
4-stage balance test				
Trial making tests	√	√	√	√
Stroop test	√	√	√	√
6-min walk test	√	√	√	√
Geriatric depression scale	√	√	√	√
Self-rating anxiety scale	√	√	√	√
Pain catastrophizing scale	√	√	√	√
Tampa scale for Kinesiophobia	√	√	√	√
Pittsburgh sleep quality index	√	√	√	√
Short-form 12	√	√	√	√
General perceived self-efficacy scale	√	√	√	√
Expenses for healthcare monthly	√	√	√	√
Expense for other diseases	√	√	√	√
Expense for low back pain	√	√	√	√
Global perceived effect		√		
Adherence		√		
Adverse Events		√		

*NRS, numerical rating scale; RMDQ, Roland Morris disability questionnaire.*

The study setting is located in the Center of Sports Medicine and Rehabilitation, Shanghai Shangti Orthopaedic Hospital (SSOH), Shanghai, China. Each participant will sign a written informed consent. This study protocol has been approved by the Ethics Committee of the Shanghai University of Sport, China (Grant number 102772019RT039).

